### Randomisation procedure and concealment of allocation

The unit of randomisation is the individual participant, who is randomly allocated using a 2:1 ratio (2 admission avoidance hospital at home: 1 inpatient admission) by a local member of the research team who accesses Sortition, the Oxford University’s Primary Care Clinical Trials Unit’s validated in-house online randomisation system. Telephone randomisation is used if sites do not have online access. A computer-generated randomisation sequence is used, and randomisation is stratified by centre, gender and by known cognitive decline [measured by the Informant Questionnaire on Cognitive Decline in the Elderly (IQCODE)] [14]. We have opted for a 2:1 randomisation ratio to deal with the concern expressed by clinical leads that a 1:1 randomisation ratio would place unmanageable pressure on the inpatient services. The success of randomisation is being measured by the number declining to be randomised or withdrawing immediately after randomisation.

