### Statistical methods

#### Sample size

We calculated the sample size for the primary outcome ‘living at home’ (the inverse of death or living in a residential care setting) at 6 months follow-up, for a 2:1 randomisation ratio with two-thirds randomised to admission avoidance hospital at home and one-third to inpatient admission. Several sources informed our estimate of effect size, these included an audit of 750 patients who received admission avoidance hospital at home in Lanarkshire, and the summary estimate from a Cochrane Review of admission avoidance hospital at home that was published in 2008 [16]. Our proposed study effect estimate is based on a control group (inpatient admission) event rate at 12 months of 50% living in a residential setting, with a 10% reduction to 40% in the admission avoidance hospital at home group, equal to a relative risk of 0.8 which lies towards the top end of the 95% confidence interval (CI) for the pooled estimate reported in the Cochrane Review [16]. We have calculated that to achieve 90% power at a significance level of 0.05, we will need to recruit 1350 participants to detect a 10% absolute difference. The estimated recruitment rate allows 15% attrition resulting in a projected sample size of 1552. We have re-examined the sample size calculation using an estimate of the intra-cluster correlation (ICC) of 0.005, this would provide 88% power to detect the assumed effect size of RR = 80%, for a two-tailed alpha of 0.05.

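### The 88% power quoted for an ICC of 0.005 charges a clustering penalty that centre-stratified individual randomisation and the stated model do not incur, and the one calculation found to return it leaves out the planned attrition

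*Protocol article*

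**What the plan says.** The Sample size section sets the calculation "for a 2:1 randomisation ratio with two-thirds randomised to admission avoidance hospital at home". It takes event rates of "50% living in a residential setting, with a 10% reduction to 40" per cent, "equal to a relative risk of 0.8", and gives 1350 as the number needed "to achieve 90% power at a significance level of 0.05". It then allows 15% attrition, which brings the projected total to 1552. The last sentence revisits the calculation: "using an estimate of the intra-cluster correlation (ICC) of 0.005, this would provide 88% power" for the same relative risk, "for a two-tailed alpha of 0.05". It does not say what the cluster is, how many clusters there are, or which total was used.

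The section on randomisation and concealment describes a design without cluster allocation: "The unit of randomisation is the individual participant, who is randomly allocated using a 2:1 ratio", and "randomisation is stratified by centre, gender and by known cognitive decline".

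The Analysis section fits participants and centres as random effects, and time, treatment and their interaction as fixed effects. It names no random treatment-by-centre term. The Setting and sample section lists eight recruiting organisations.

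**The concern.** An ICC inflates the variance of a treatment comparison when whole clusters go to one arm, because differences between clusters are then mixed with the difference between treatments. Here every centre contributes to both arms and the model carries a centre intercept. A centre with generally good or poor outcomes shifts both arms together and drops out of the comparison. A loss of power attributed to an ICC of 0.005 therefore does not fit the randomisation and model described in the same document.

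The 88% is the last power figure given and the one likely to be quoted. If the ICC stands for ordinary centre differences, the figure is too low. If it stands for variation in the treatment effect between centres, the primary model lacks the matching term, and the figure must be checked against the number left after attrition.

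**Working it through.** **Inputs.** From Sample size: control 50%, hospital at home 40%, 2:1 allocation, two-sided 0.05, ICC 0.005, totals 1350 and 1552, attrition 15%. From Setting and sample: eight centres, counted from the list. Assumption: equal centre sizes.

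**Formula.** Power = Φ[(0.10 − 1.96·SE0)/SE1], where SE0 = √[p̄(1 − p̄)(1/nH + 1/nC)] and SE1 = √[0.24/nH + 0.25/nC]. Here nH and nC are the (effective) numbers in hospital at home and inpatient care, and p̄ is their weighted event rate.

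**Step 1: the protocol's own figure.** Treat each centre-by-arm cell as an independent cluster, eight per arm, with all 1552 analysed.
- Hospital at home: 1034.7 participants, 129.3 per cluster. Design effect 1 + 128.3 × 0.005 = 1.642; effective number 630.3.
- Inpatient: 517.3 participants, 64.7 per cluster. Design effect 1 + 63.7 × 0.005 = 1.318; effective number 392.4.
- p̄ = 0.4384, SE0 = 0.03191, SE1 = 0.03190. Power = Φ(1.174) = **88.0%**.

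This matches the stated value.

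**Step 2: the same formula after attrition.** 1552 × 0.85 = 1319.
- Design effects are 1.545 and 1.270; effective numbers are about 569 and 346.
- SE0 = 0.03381, SE1 = 0.03382. Power = Φ(0.997) = **84.1%**.
- At 1350 the same route gives 84.7%.

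**Step 3: what Step 1 assumes.** Independent clusters in each arm mean that a centre's two arms vary separately, so the treatment effect differs between centres. With p̄ = 0.4333, the implied variance of that effect is 2 × 0.005 × 0.4333 × 0.5667 = 0.00246. The SD is about 0.05, or 5 percentage points around a 10-point mean effect. Adding 0.00246/8 to the squared standard errors of an individually randomised comparison gives 87.9% at 1552 and 84.0% at 1319, which agrees with Steps 1 and 2. The Analysis section has no term for this variation.

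**Step 4: the design and model as described.** With individual allocation within centre, a centre intercept and a common treatment effect, the between-centre share of the variance is removed and the rest is multiplied by (1 − 0.005) = 0.995. For 1350 analysed (900 and 450), SE0 falls from 0.02861 to 0.02854 and SE1 from 0.02867 to 0.02860. Power moves from Φ(1.532) = 93.7% to Φ(1.541) = 93.8%.

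| Analysed | Origin | No ICC | Within-centre, ICC 0.005 | Eight clusters per arm |
|---|---|---|---|---|
| 1552 | no attrition | 96.3% | 96.4% | 88.0% |
| 1350 | as stated | 93.7% | 93.8% | 84.7% |
| 1319 | 1552 × 0.85 | 93.2% | 93.3% | 84.1% |
| 1148 | 1350 × 0.85 | 89.6% | 89.8% | 80.2% |

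In no row does the ICC lower power under the stated design and model. The choice of analysed number matters more than the ICC does.

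**The case against.** The best defence is that clustering within arm is a real issue even when individuals are randomised. Each arm's care is delivered by local teams. The Interventions section says that some elements of hospital at home exist only at some sites and that about 80% of controls will receive specialist-led geriatric care. The stated objective refers to settings where provision varies. An author with that in mind could reasonably compute power with clusters in each arm. This stands as a possible intention. It does not rescue the figure, because the model omits the matching variation and the calculation uses the full recruited total.

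A second defence is that 88% is only a re-examination, errs low under the stated model, and changes no sample size. That is true, and it limits the consequence.

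A third is that a condensed article may leave cluster details to the full protocol. That is also fair. The point here is the printed figure's conflict with the design and model, not the missing detail.

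A reader might infer that 88% cannot be derived from the document at all. Step 1 shows that it can. That inference comes from treating a whole centre, both arms together, as one cluster, which the document does not say.

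**Conclusion.** The 88% is not the power of the trial as described. Under the stated allocation and model an ICC of 0.005 costs essentially nothing, and power is 93.8% with 1350 analysed or 93.3% with 1319, so 88% is 5 to 6 points too low. Under the reading that returns 88.0%, the planned attrition brings it to 84.1%, so the figure is about 4 points too high and the model lacks the term it presupposes.

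If 1350 is the number recruited and 15% are lost, power is 89.8%, within 2 points of the stated value. The ICC plays no part in that shortfall: power without it is 89.6%. Any replacement figure must therefore name its analysed number.

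A reader might also infer that the trial is underpowered. The document does not support this: on the stated model the error understates power.

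These results take the stated 50% and 40% as given, count eight centres from the list, assume equal centre sizes and use an unadjusted two-proportion approximation. The origin of the 88% is inferred from the numerical match and is not documented.

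**What to change.** Choose one of two routes.

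1. If ordinary centre differences were meant, replace the 88% with a statement that, under individual allocation stratified by centre and a centre term in the model, an ICC of 0.005 does not reduce power. Give the power at a named analysed number, for example 93.3% at 1319 under the stated rates. This costs one sentence.
2. If variation of the treatment effect between centres was the concern, say so. State the clusters assumed, their number and size, and the between-centre variance of the effect. Give the power at the post-attrition number (about 84% on the apparent formula). Add a random treatment-by-centre term to the primary model. This costs a few sentences and a model change, which should be settled before outcomes are seen by arm. With eight centres the added variance will be estimated imprecisely.

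Neither route changes the randomisation or data collection.

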### Analysis

We will analyse the data using an intention-to-treat analysis and based on a mixed effect model adjusting for recruitment centre (random effects) and individual patient characteristics. For the primary outcome of living at home 6 months, the primary analysis we will use a mixed-effect logistic regression model including data available on all randomised patients at 6 months and 12 months follow-up, adjusting for recruitment centre, gender, and IQCODE score at baseline. In the model, participants and centres will be fitted as random effect, and time and treatment as fixed effect. We will fit an interaction term between time and intervention group so that possible differences of intervention effect could be assessed at each time point. Although, the method has the advantage of implicitly accounting for the data missing at random mechanism, we will also assess the impact of missing data on the primary analysis by carrying out sensitivity analyses based on imputing (multiple imputation) the missing values. We will use similar models for all binary outcomes (presence of delirium, cognitive impairment, etc.), and will use equivalent models for continuous outcomes (e.g. normal distribution). We expect length of stay to be highly skewed so other parametric models might be required for this, and in the case of poor fit we will use simple non-parametric tests (non-adjusted) for this outcome. We have planned one subgroup analysis of the effect of care setting (home versus hospital) on the incidence of delirium in people who are cognitively impaired (defined by the MoCA) [10].

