## Background

Older people are being admitted to hospital as an emergency in increasing numbers [1]. From a system perspective this trend is not sustainable, and from a patient perspective there are many reasons to question whether a hospital is the best place of care for older adults with frailty. There is some evidence to indicate that hospital care might be potentially harmful to older people due to a lack of mobility that can increase the risk of disability from frailty [2]. The high cost of hospital-based care has also been a major driver to innovate in an economic climate that does not allow for the expansion of hospital bed numbers to match the growth in admission numbers [3]. Avoiding admission to hospital by the provision of hospital-level care in the home is a model of healthcare that is being considered in many countries [4, 5] as hospitals deal with the rise in emergency admissions. However, the scale to which these models of care have transformed health systems is limited, reflecting the lack of evidence to underpin decision-making.

A meta-analysis of randomised trials of admission avoidance hospital at home is limited by the small number of small randomised controlled trials. The evidence suggests that these types of service, that include the option of transfer to hospital, may provide an effective alternative to inpatient care for a select group of older people who require hospital admission [4]. The lack of data on cost-effectiveness also limits the extent to which these types of service form part of a wider policy strategy for acute hospital-level care. It is possible that avoiding admission to hospital reduces the risk of delirium in older people who require hospital-level healthcare. Delirium, a frequent and serious complication in older people who develop an acute illness, is associated with adverse consequences which include increased risk of hospital-acquired complications, new admission to institutional care, new dementia, increased hospital length of stay and increased mortality [6, 7].

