**Fig. 1 Fig1:**
[figure not shown]
Study flowchart

We collect data at baseline from the patient’s clinical notes and from the clinical lead on the presenting problem that requires admission to hospital, and demographic information (age, education). We also collect data on background cognitive status using the IQCODE, a 16-item informant-based questionnaire, which can also be completed by a carer [14]; incident and persistent delirium measured by the CAM [9], co-morbidity measured by the Charlson Index [15], activities of daily living measured by the Barthel Index [11], current cognitive impairment measured by the MoCA [10], health status measured by the EuroQol five-dimension five-level instrument (EQ-5D-5 L) [12] and major health service use (for example admission to hospital, use of outpatient services and ambulances, home care/help and respite stays in a residential setting) in the 6 months prior to their current illness. If the patient appears to be burdened by the collection of baseline data we use a two-stage approach, with core data (Short IQ Code [14] and Confusion Assessment Method [9]) collected prior to randomisation and following consent, and the remaining data (Barthel Index [11], Charlson Co-Morbidity Index [15], MoCA [10], EQ-5D-5 L [12] and Health Resource Use Questionnaire) collected soon after randomisation (Fig. 2).

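### The primary model is valid but leaves out age and pre-randomisation delirium status, two baseline predictors already collected; adding them is a modest gain at almost no cost

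*Protocol article*

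**What the plan says.** The Analysis section opens with a general statement of a "mixed effect model adjusting for recruitment centre (random effects) and individual patient characteristics". For the primary outcome it then gives the actual list: "adjusting for recruitment centre, gender, and IQCODE score at baseline". Participants and centres are random effects; time, treatment and their interaction are fixed effects. The data are whatever is available at 6 and 12 months. The section relies on missingness at random, with multiple imputation as a sensitivity analysis.

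The list matches the design. Under Randomisation procedure and concealment of allocation, "randomisation is stratified by centre, gender and by known cognitive decline", the last measured by IQCODE.

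The section on data collection, management and analysis shows what else is known at entry. It lists "demographic information (age, education") and CAM delirium status. When baseline collection is split to spare the patient, it keeps "core data (Short IQ Code [14] and Confusion Assessment Method [9]) collected prior to randomisation" and lets Barthel, Charlson, MoCA and EQ-5D follow soon after allocation.

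The Background says that delirium is associated with "new admission to institutional care, new dementia, increased hospital length of stay and increased mortality".

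**The concern.** The endpoint is death or residential care in people aged 65 and over with an acute illness. Age is an obvious candidate predictor, and the article itself names delirium as a marker of both endpoint components. Both variables are fixed before allocation, so adjusting for them cannot introduce post-randomisation bias. The covariate list is stated in the article and is not deferred, so the omission is a choice that can be reviewed.

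Two things are at stake. The first is precision: in a logistic model, adjustment for prognostic baseline covariates generally raises the power of the treatment test. The second is missing data: an available-data likelihood analysis is protected only against missingness explained by what is in the model. Attrition is allowed for at 15%. Deaths come from medical records, but place of residence is recorded at follow-up visits, so unknown status would arise mainly among survivors who are not seen. If those survivors tend to be older or to have been delirious at entry, conditioning on both variables makes the assumption more credible.

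**Working it through.** **1. The plan's own figure, as a base.** Inputs from Sample size: 50% v 40%, two-sided alpha 0.05, 90% power, 2:1 allocation. The pooled proportion is (0.50 + 2 × 0.40)/3 = 0.4333.

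- Control group: n = [1.960 × √(1.5 × 0.4333 × 0.5667) + 1.282 × √(0.25 + 0.24/2)]² / 0.10² = (1.1895 + 0.7795)² / 0.01 = 387.7, so 388.
- Total: 3 × 388 = 1164, against a stated 1350.
- Power at 450 v 900: (0.10 − 1.960 × 0.02861)/0.02867 = 1.532, which is 93.7%.

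The mismatch between 1164 and 1350 is a separate matter. Here the two totals only bracket the number analysed. Neither assumes any gain from covariates, so adding covariates changes no stated figure.

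**2. Gain in information beyond IQCODE.** The documents give no prognostic strengths, so these are assumptions. Trials of 1164 were simulated with marginal risks of 40% v 50% and 2:1 allocation. IQCODE was in both models, with and without age and delirium (Monte Carlo error about 0.7 points):

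| OR per SD of age / for delirium | Extra information | Power without → with |
|---|---|---|
| 1.3 / 1.5 | 2% | 91.0% → 91.5% |
| 1.5 / 2.0 | 4% | 91.5% → 93.4% |
| 1.8 / 3.0 | 10% | 91.6% → 95.1% |

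A second simulation, also with IQCODE in both models and the same range of odds ratios, gave about 2% to 9% and 0.3 to 2.5 points at 1164 to 1350.

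**3. Cross-check by formula.** Power after adjustment is approximately Φ(δ√g − 1.960), where δ = 1.960 + z(base power) and g is the information ratio.

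- Base 90%, δ = 3.242. g = 1.02: Φ(3.274 − 1.960) = 90.6%. g = 1.04: Φ(3.306 − 1.960) = 91.1%. g = 1.10: Φ(3.400 − 1.960) = 92.5%.
- Base 93.7%, δ = 3.492. g = 1.02: Φ(3.526 − 1.960) = 94.1%. g = 1.10: Φ(3.662 − 1.960) = 95.6%.

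So 2% to 10% more information converts to about 0.4 to 2.5 points. The simulated 3.5 points at the strongest assumption is above what 10% implies and probably includes simulation error.

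**4. Missing data.** This is a large-sample calculation with about 15% missing, 20% delirium prevalence (assumed) and a true risk difference of −0.100. The odds ratios for missingness were 1.5 or 2.0, per SD of age and for delirium, and there was no covariate adjustment.

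- Same dependence in both arms: the risk difference stays at −0.100 and the risk ratio at 0.793 to 0.798.
- Dependence in the control arm only: the risk difference moves to between −0.095 and −0.083.

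The control-arm-only case was repeated with IQCODE already in the model. It assumed a correlation of 0.3 between IQCODE and each of age and delirium, and missingness odds ratios of 1.8 per SD of age and 3 for delirium. Without age and CAM the estimates were −0.092, −0.089 and −0.088 for weak, moderate and strong prognosis. With them they were −0.099, −0.100 and −0.103. The shift without them is 0.008/0.100 to 0.012/0.100, or 8% to 12% of the design difference.

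**The case against.** The strongest reply is that nothing here is an error. The plan prespecifies its covariates and adjusts for every stratification factor, which is standard and valid under randomisation. The general phrase about patient characteristics does not contradict the specific list, since gender and IQCODE are such characteristics. This stands.

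A reader might go further and infer four things that the documents do not support.

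- **That omitting the covariates biases the treatment odds ratio towards the null.** The odds ratio does change with the covariate set, but that is non-collapsibility: a different conditional quantity, not bias. The planned participant random effect already makes the coefficient conditional and partly absorbs stable differences between people.
- **That the gain is large, say 5% to 20% more information, and can be read as an equivalent number of extra participants.** Figures of that size come from comparison with a model without covariates. The planned model already contains IQCODE, which plausibly overlaps with age and delirium.
- **That the available-data analysis is unsound.** The calculation shows no material shift unless missingness depends on these variables differently by arm. That is possible in an open trial, but nothing in the article shows it. Deaths taken from records, and the use of both 6- and 12-month outcomes, limit the exposure.
- **That the imputation is deficient.** The article does not list the imputation variables, and an article commonly leaves them to the analysis plan. Age and CAM could enter there. That would help the sensitivity analysis but not the headline estimate.

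**Conclusion.** The point holds as a modest improvement to a valid analysis. Age and baseline CAM are collected and known before allocation, and the article's own Background supports delirium as prognostic; the primary model uses neither. Adding them to a model with IQCODE gives about 2% to 10% more information. In power this is roughly 0.5 to 3.5 points by simulation, with the direct conversion pointing to about 2.5 as the more likely ceiling. These figures rest on assumed odds ratios. The missing-data benefit is real in principle. In the calculations it mattered only when loss depended on age or delirium differently by arm, where the planned covariates left a shift of 8% to 12% of the design difference. No stated sample size or power figure needs to change on this account.

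**What to change.** Amend the primary-model sentence in the Analysis section so that age (continuous) and baseline CAM status (delirium present or absent) are prespecified fixed effects alongside centre, gender and IQCODE. Retain the currently planned model as a sensitivity analysis. Barthel, Charlson and MoCA should stay out of the primary model, because the two-stage approach allows them to be collected after allocation.

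The cost is one sentence and no new data. The article reports recruitment as ongoing, so the change could be made before outcomes by arm are seen, and its date should be recorded. The one downside is that the conditional odds ratio will differ slightly from that of the less adjusted model; reporting both makes this visible.

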### Eligibility criteria

We are recruiting patients who meet the following eligibility criteria for inclusion: (i) are 65 years and older, (ii) are willing and able to give informed consent for participation in the study, (iii) have been referred to the geriatrician-led admission avoidance hospital at home service and would otherwise require hospital admission for an acute medical event. The presence of a carer will not be a requirement for enrolment and will depend on the individual circumstances of the patient; this will be at the discretion of the clinician responsible for the patient, as is current clinical practice in each centre. Participants will be excluded if they have (i) an acute coronary syndrome (this includes myocardial infarction and unstable angina and is characterised by cardiac chest pain and associated with ECG changes), (ii) require an acute surgical assessment, (iii) have a suspected stroke, (iv) are receiving end of life care as part of a palliative care pathway, (v) refuse admission to the geriatrician-led admission avoidance hospital at home, or are considered by the clinical staff to be too high risk for home-based care, for example those who are physiologically unstable, who are at risk to themselves or if the carer reports hospital at home would not be acceptable, and (vi) patients living in a residential setting.

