### Outcome measures

#### Primary outcome

We are collecting data for each patient on ‘living at home’, defined as the inverse of death or living in a residential care setting, at 6 months follow-up from randomisation.

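### The primary model's participant random intercept yields a subject-specific odds ratio that is not comparable with the planned RR of 0.8 or 10-point difference unless it is standardised

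*Protocol article*

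**What the plan says.** All references are to the protocol article.

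- **Primary outcome:** living at home is "defined as the inverse of death or living in a residential care setting, at 6 months follow-up from randomisation". Eligibility criteria exclude "patients living in a residential setting", so everyone starts free of the event.
- **Analysis:** the primary analysis is a "mixed-effect logistic regression model including data available on all randomised patients at 6 months and 12 months follow-up", adjusted for centre, gender and baseline IQCODE score. It continues: "In the model, participants and centres will be fitted as random effect, and time and treatment as fixed effect". On the time-specific effect it says: "We will fit an interaction term between time and intervention group". The stated reason for the joint model is that it deals implicitly with data missing at random; multiple imputation is a sensitivity analysis.
- **Sample size:** planning uses population risks. It takes a control "event rate at 12 months of 50% living in a residential setting", reduced to 40% (a relative risk of 0.8), with the trial sized "to detect a 10% absolute difference". The effect is set against a pooled estimate from a systematic review.
- **Research objective:** the primary aim is to estimate effectiveness.

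The article names no risk ratio, risk difference or standardisation step that would connect the fitted model to the planning effect.

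**The concern.** A participant random intercept makes the treatment effect conditional on the person's own latent risk. When within-person correlation is modest, the conditional and population odds ratios are close. Here they are not. Everyone who has died by 6 months is still an event at 12 months, and most people in residential care at 6 months are likely to be there at 12. Two nearly concordant binary values per person push the intercept variance up, and the treatment coefficient grows with it.

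The size of the coefficient would then depend heavily on how many people return home between the visits, which is not a feature of the treatment effect at 6 months. It would also depend on how the software integrates over the intercept. Readers who set such an odds ratio beside the planning effect, or beside the review's pooled estimate, would be comparing different quantities.

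**Working it through.** **Planning effect.** Relative risk = 0.40/0.50 = 0.80; difference = 10 points. Both match the Sample size section. The marginal odds ratio is (0.40/0.60)/(0.50/0.50) = 0.667. The step from 0.80 to 0.667 is only odds ratio versus risk ratio and would occur in any logistic model.

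**Inputs.** From the protocol: two visits, participant random intercept, time, treatment, time-by-treatment interaction, 2:1 allocation, and the 50% v 40% contrast. Assumed, because the document does not give them: the 6-month rates where they differ from 50% v 40%, the 12-month rates in scenario A, and the share *r* of 6-month events reversed (back home) by 12 months. Centre and covariates are left out to isolate the participant intercept.

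**Model.** With Y = 1 for death or residential care, arm A, visit t and u ~ N(0,1): logit P(Y = 1 | u) = β_t + δ_t·A + σ·u. The 6-month conditional odds ratio is exp(δ_6).

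**Expected pattern shares per arm.** Event at both visits: p6(1 − r). At 6 months only: p6·r. At 12 months only: p12 − p6(1 − r). Neither: the remainder. For example, with 50% at 6 months, 60% at 12 months and r = 5%, the control shares are 0.475, 0.025, 0.125 and 0.375. With 40% and 50%, the hospital-at-home shares are 0.38, 0.02, 0.12 and 0.48.

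**Maximum likelihood by dense-grid integration.** Odds ratios are for the event; the odds ratio for living at home is the reciprocal.

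- Scenario A: 50% v 40% at 6 months, 60% v 50% at 12 months. Marginal 6-month odds ratio 0.667.
- Scenario B: 40% v 32% at 6 months, 50% v 40% at 12 months. Marginal 6-month odds ratio (0.32/0.68)/(0.40/0.60) = 0.706.

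| r | A: SD of intercept | A: 6-month OR | B: SD of intercept | B: 6-month OR |
|---|---|---|---|---|
| 20% | 2.5 | 0.46 | 3.1 | 0.46 |
| 10% | 4.4 | 0.30 | 5.2 | 0.30 |
| 5% | 6.6 | 0.17 | 7.7 | 0.18 |
| 2% | 9.8 | 0.08 | 11.3 | 0.08 |

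The true 6-month RR is 0.80 in every row. With lower 6-month rates (35% v 28%, marginal odds ratio 0.722) the values are 0.51, 0.38, 0.27 and 0.16.

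**Hand check.** The usual approximation is conditional log OR ≈ marginal log OR × √(1 + 0.346σ²). For scenario A at r = 10%: −0.405 × √(1 + 0.346 × 4.4²) = −0.405 × 2.77 = −1.12, an odds ratio of about 0.33. The exact fit gives 0.30.

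**Dependence on integration (scenario A, 6-month OR).**

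| r | Laplace | 7-point adaptive | 15-point adaptive | Dense grid |
|---|---|---|---|---|
| 10% | 0.36 | 0.32 | 0.30 | 0.30 |
| 5% | 0.21 | 0.26 | 0.18 | 0.17 |
| 2% | 0.13 | 0.17 | 0.11 | 0.08 |

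In scenario B with few reversals, Laplace fits did not settle on reproducible values, so none are quoted.

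**Back to the population scale.** Averaging the dense-grid fit over u gives 6-month risks of 0.50 v 0.40 in scenario A (RR 0.80) and 0.401 v 0.319 in scenario B (RR 0.795, difference 8.2 points against a true 8).

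**The test.** In 250 simulated trials per setting (440 v 880 participants, scenario A rates, r = 5%), the likelihood-ratio test of the 6-month effect had 95.2% power and 4.8% type I error. A plain 6-month logistic comparison gave the same two figures.

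**The case against.** - **The model contains the design quantity.** This stands. Integrating over the random intercept recovers an RR of about 0.80 and nearly the right risk difference. A reader might infer that the planned model cannot deliver the effect the trial was sized for. That is true only of the unstandardised odds ratio.
- **The article does not say an odds ratio will be reported.** This also stands. A reader might infer that a modest benefit will be published as a huge odds ratio, but the Analysis section fixes the model and names no effect measure. A standardised summary and the quadrature settings could properly sit in an analysis plan that is not shown. What the article does fix is the participant random effect, and the point rests on that.
- **Inference is intact.** It is, for the likelihood-ratio test with accurate integration. Nothing here supports reading the p-value as invalid. A Wald test would need properly computed standard errors: one run with the optimiser's rough standard errors rejected 20.4% of the time under the null, which reflects those standard errors and is not evidence against the model.
- **Instability is partly a matter of effort.** At 10% and 5% reversal, 15-point quadrature is close to the dense grid. At 2% a gap remains (0.11 v 0.08).
- **The drama depends on assumed reversal.** At 20% the odds ratio is 0.46 against a marginal 0.67 to 0.71: still displaced, but much less so.
- **The joint model has a purpose.** Its handling of missing data is a legitimate reason to keep it, so replacing it is not the only remedy.

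**Conclusion.** The point holds as one about the effect estimate. For a fixed 6-month RR of 0.80, the conditional odds ratio ranges from 0.46 to 0.08 in scenarios A and B as assumed reversal falls from 20% to 2%, against a marginal odds ratio of 0.67 to 0.71. On the living-at-home scale that is about 2.2 to 12.5 (1/0.46 to 1/0.08), against 1.4 to 1.5. Below 10% reversal the figure also moves appreciably with the integration method.

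The sizes rest on the assumed rates and reversal shares. The direction does not change over the range examined, and the irreversibility of death needs no assumption. Because the population effect can be recovered and the test is sound, this should be fixed but does not undermine the trial.

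**What to change.** **Preferred.** Define the primary estimate as the population-average 6-month risk ratio and risk difference, each with a 95% confidence interval, adjusted for centre, gender and IQCODE. Estimate them from a 6-month model without a participant random intercept: modified Poisson regression with robust standard errors, or logistic regression followed by marginal standardisation. A centre effect can stay. Analyse 12 months separately with the same model, or jointly with 6 months by GEE. Use 12-month status in the imputation model for missing 6-month outcomes.

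**Alternative.** If the joint mixed model is kept for its missing-at-random handling, make the primary effect estimate the RR and risk difference standardised over the random effects. State the integration method in advance: adaptive quadrature with enough points that adding more does not change the result, and not Laplace.

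**Cost.** A change of analysis wording, best made before unblinding; recruitment is still described as ongoing. The preferred option gives up the implicit borrowing from 12-month data, which the imputation model largely replaces. The alternative needs some extra computation.
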